### 2.4. Study Setting and Recruitment

The research will be conducted in the maternity wards of three affiliated hospitals in X University, where each hospital has an annual baby-birth record of more than 4000. All women admitted in the wards will be approached by researchers to ask their willingness and will be measured by the EPDS before recruitment. If they have an EPDS of 10 or more, they will be eligible to participate in this study. The information sheets, posters, and leaflets will be used to introduce the purposes and process of the research before recruitment. If rural-to-urban floating women meeting the inclusion criteria are willing to participate, they will be asked to sign an informed consent form and be informed of freedom to withdraw whenever they want. The CONSORT (consolidated standards of reporting trials) [48] flowchart is illustrated in Figure 1. The recruitment period is expected to extend over a 3-month period. Recruitment of participants began in May 2022. Primary endpoints (baseline and postintervention), follow-up measure (three months), and data analysis are expected to be complete in January 2023.

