### 2.5. Sample Size

The study sample size will be determined by the primary outcome of PPD, with the standardized effect size of 0.35 for PPD (EPDS scores) reported in a previous PPD trial [49,50]. A sample of 180 women (90 women per group) will be needed to detect an effect size of at least 0.35, with 80% power, two-sided *p* < 0.05, which is calculated by inputting the above parameters in PASS (Power Analysis and Sample Size) software (NCSS company, East Kaysville, UT, USA). Assuming an attrition rate of about 20%, a minimum of 226 women (113 in each group) is required.

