#### 2.8.2. Primary Outcome

Postpartum depression symptoms as the primary outcome will be measured with the Chinese version of the Edinburgh Postnatal Depression Scale (EPDS). EPDS is composed of ten items and each item scores from 0 to 3 [55]. The total score ranges from 0 to 30, and the higher score indicates the more serious depressive symptoms. The reported internal consistency of the Chinese version EPDS was 0.87, and its concurrent validity was 0.79 with the BDI (Beck Depression Inventory) [56]. The total EPDS score of 10 or more is recommended as the presence of clinically relevant depressive symptoms in mainland China [56].

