### 2.10. Data Analysis

All the statistical analyses will be conducted by the Statistical Package for Social Sciences (SPSS). Descriptive analysis will be undertaken to describe the social-demographic and clinical data. Mean, standard deviation, and frequencies, as well as percentages will be used for continuous data and categorical data, respectively. The chi-square (χ^2^) for categorical variables, and the independent sample *t*-test for continuous variables will be conducted to detect any significant difference on social-demographic and clinical characteristics and baseline outcomes between the intervention group and the control group. The effect of intervention on reduced PPD symptoms and stigma and on improved social support, quality of life, and mother–child bonding across the three time points will be evaluated via repeated measures multivariate analysis of covariance to explore how outcomes have changed between groups, over time, and the interaction between group and time. The independent *t*-test will be used to compare satisfaction with the health care that they received in the postpartum period between the intervention group and the control group on the time point of immediately after the intervention. A *p* value less than 0.05 will be considered statistically significant.

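### EPDS is the sole primary outcome and the basis of the sample size, but the analysis takes it together with four secondary outcomes in a repeated-measures MANCOVA and names no EPDS test, time point or deciding effect

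*Protocol article*

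**What the plan says.** Section 2.8.2 names one primary outcome: "Postpartum depression symptoms as the primary outcome will be measured with the Chinese version of the Edinburgh Postnatal Depression Scale (EPDS").

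Section 2.5 sizes the trial on it: "The study sample size will be determined by the primary outcome of PPD". The assumed difference enters the calculation as follows: "with the standardized effect size of 0.35 for PPD (EPDS scores) reported in a previous PPD trial". The result is then given: "A sample of 180 women (90 women per group) will be needed to detect an effect size of at least 0.35". The power and error rate behind that figure are stated in the same place: "with 80% power, two-sided *p* < 0.05".

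Section 2.10 lists depressive symptoms, stigma, social support, quality of life and mother–child bonding in one sentence. Over the three visits, it says, the effect on this list "will be evaluated via repeated measures multivariate analysis of covariance to explore how outcomes have changed between groups, over time, and the interaction" of group and time. The section closes with a single threshold, which applies to every test: "value less than 0.05 will be considered statistically significant". Satisfaction with care is handled separately, by a t-test after the intervention.

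The nearest thing to a primary time point is in the timetable in section 2.4: "Primary endpoints (baseline and postintervention), follow-up measure (three months"). Section 2.10 does not return to it. The note to Table 2 places baseline before randomization.

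**The concern.** The primary outcome, the sample size and the analysis should all address the same question. Here the first two concern EPDS alone, while the third concerns five outcomes and three kinds of effect.

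A joint multivariate test asks whether any of the five outcomes differs between groups. It can be significant because of social support or stigma with no change in EPDS. It can also miss a real EPDS effect.

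If the sentence instead means one model per outcome, EPDS has its own tests, but there are three effects to read (group, time, group-by-time) and nothing says which one decides. The time effect does not compare treatments. The group effect over three visits, if baseline is one of them, averages in a pre-randomization value at which no difference is expected.

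Either way, the trial has no fixed criterion for success on its primary outcome, and the choice could be made after the results are seen.

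**Working it through.** **Inputs from the protocol.** n = 90 evaluable women per group, d = 0.35 on EPDS, two-sided 0.05 (2.5); five outcomes, three time points (2.10).

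**Assumptions, because the article gives no correlations.** The effect is equal at both post-baseline visits. The correlation between visits is ρ = 0.5 unless stated otherwise. The between-outcome correlation r runs from 0 to 0.6, equal for all pairs, with every outcome scored so that higher means better.

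**The plan's own figure.** A two-sample comparison needs 2 × ((1.96 + 0.84)/0.35)² ≈ 128.1, so 129 per group; 90 per group gives 65% power. The stated 90 therefore does not follow from the stated inputs without a baseline adjustment (correlation about 0.55), which the article does not mention. The attrition step does reproduce: 90/0.8 = 112.5, so 113 per group and 226 in all. The sample size is a separate matter; 90 is used below as stated.

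**EPDS alone, group-by-time (2 df).** Noncentrality λ = (n/2) × d² × 2/(3(1 − ρ)) = 45 × 0.1225 × 1.333 = 7.35. The noncentral F with (2, 177) df gives 67% power.

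**Joint group-by-time test, five outcomes (10 df).** λ = 7.35 × k, noncentral F with (10, 169) df. The factor k depends on which outcomes respond:

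- EPDS only: k = (1 + 3r)/((1 − r)(1 + 4r))
- the other four only, each d = 0.35: k = 4/((1 − r)(1 + 4r))
- all five, each d = 0.35: k = 5/(1 + 4r)

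| r | EPDS only: λ, power | Other four only: λ, chance significant | All five: λ, power |
|---|---|---|---|
| 0 | 7.35, 38% | 29.4, 98% | 36.8, 99% |
| 0.3 | 9.07, 47% | 19.1, 85% | 16.7, 79% |
| 0.5 | 12.25, 62% | 19.6, 86% | 12.25, 62% |
| 0.6 | 15.13, 74% | 21.6, 90% | 10.8, 56% |

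The middle column is the main result. EPDS is unaffected throughout, yet the joint test is significant in about 85–98% of trials. The outer columns, set against 67% for EPDS alone, show that the joint test can have more or less power depending on the pattern of effects.

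**One model per outcome: three possible EPDS analyses at ρ = 0.5.**

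- Group main effect over three visits: difference 0.35 × 2/3 = 0.233; SD of the three-visit mean √((1 + 2ρ)/3) = 0.816; ratio 0.286; λ = 45 × 0.286² = 3.67; power 48%.
- Group-by-time: 67%, as above.
- Postintervention, adjusted for baseline: 0.35/√(1 − 0.25) = 0.404; Φ(0.404 × √45 − 1.96) = Φ(0.75) = 77%.

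The same formulas give 57%, 52% and 69% at ρ = 0.3, and 41%, 88% and 91% at ρ = 0.7. The choice of effect matters at each value.

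On this reading there are also five outcomes at 0.05. If they were independent, the chance of at least one false positive for a single effect would be 1 − 0.95⁵ = 23%; positive correlation lowers it.

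**The case against.** The strongest reply is that this is a condensed article, and that section 2.10 leaves out one clarifying sentence which an analysis plan may contain. That would hold if the article were silent. It is not: it states a method, and that method does not isolate the outcome the article calls primary.

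Four stronger readings may tempt a reader, and the documents do not support them.

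- **That the MANCOVA is the only efficacy analysis.** It is the only one covering EPDS. Satisfaction, which is part of the third hypothesis in 2.1, has its own t-test.
- **That a single joint model is stated.** It is the natural reading of a multivariate method applied to five listed outcomes, but the text never says one model. A model per outcome is possible, and EPDS would then be tested by itself. The joint-test figures and the 23% belong to alternative readings and cannot be added together.
- **That the joint test generally dilutes an EPDS effect.** For an EPDS-only effect, its power is below 67% at r up to 0.5 and above it at r = 0.6. If all five outcomes improve, as 2.1 hypothesises, its power is higher than EPDS alone at low r and lower at high r. EQ-5D has an anxiety/depression dimension (2.8.3), so zero correlation is unlikely.
- **That the analysis ignores postintervention.** It is one of the three time points analysed, but it is not singled out. The phrase in 2.4 sits in a timetable sentence and is loose wording rather than an endpoint definition.

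It is also fair to say that a multiplicity adjustment for the secondary outcomes, and whether to keep a multivariate analysis among them, are matters of preference or of the analysis plan. None of this supplies the missing primary test.

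**Conclusion.** The concern holds in a limited form. Section 2.10 does not say which EPDS comparison, at which time point, decides the trial, and the method it states is mismatched to a single primary outcome on which the sample size rests.

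The joint reading fails for a reason that does not depend on power loss: a significant result is not evidence about EPDS. The per-outcome reading leaves a choice that moves EPDS power by 29 percentage points (48% to 77%) at a time correlation of 0.5.

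The percentages rest on the assumed correlations, equal effects at both post-baseline visits and 90 evaluable women per group. The mismatch itself rests only on the text.

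**What to change.** - **Section 2.10:** state one primary test, the between-group difference in EPDS total score at postintervention, from a model for EPDS alone adjusted for baseline EPDS, at two-sided 0.05.
- **Section 2.10:** label EPDS at the three-month follow-up, STIG-9, PSSS, EQ-5D, PBQ and satisfaction as secondary. A multivariate analysis may stay if it is labelled secondary too.
- **Section 2.4:** remove baseline from the primary endpoints, since it is measured before randomization.

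The cost is rewording one paragraph and one phrase. No new data are needed, and the model runs in the software already named. The secondary outcomes no longer count towards the primary conclusion. The change should be made and dated before outcomes are compared by group. It does not resolve the separate question of how 90 per group was obtained.

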### 2.11. Ethical Consideration

The plan and the design content have been reviewed and approved by the Institutional Review Board of the University. This study will adhere to the ethical standards of the Declaration of Helsinki for the whole procedure. Information of all participants will be confidential and anonymized and only be treated at a collective level.

### 2.12. Validity and Reliability

The scientific and rigorous research design, i.e., the sound theoretical framework of intervention, a good representative and predetermined sample, and all the tools with a proven good reliability and validity, will be strictly executed to reduce bias effectively and enhance the generalizability of the research results beyond the target population. Furthermore, to ensure proper administration of the interventions, the related researchers will be trained before data collection. Moreover, the group allocation will be blind to the participants, enrolling researchers, outcome assessors, and data analysts in order to reduce the bias during the research process.

## 3. Discussion

Nowadays, the high prevalence of PPD for rural-to-urban floating women [44,45] and the shortage of mental health service resources in China [23] make it extremely urgent to effectively intervene in PPD for floating women. Despite the existence of various interventions, only a small number of women have sought professional help to reduce their depressive symptoms after childbirth [21], suggesting the need for an innovative intervention delivery to overcome women’s help-seeking barriers. Online and offline (OTO) intervention is the combination of face-to-face treatment with internet-based interventions that have significant benefits [7]. On the one hand, it can have higher flexibility and accessibility, and reduced financial and time cost [27]. On the other hand, it likewise can offer significant customization via face-to-face communication and support [7]. Therefore, our research aims to examine the effectiveness and acceptability of an OTO intervention of the “Hi, Mom” program on psychosocial outcomes for Chinese rural-to-urban floating women, including the reduction of PPD symptoms and PPD stigma, and the improvement of social support and quality of life. To the best of our knowledge, no RCTs by OTO intervention have been conducted targeting PPD in China.

Despite the advantages of the research, some limitations need to be noted. Firstly, self-report tools will be used to measure PPD, and it may lead to social desirability bias owing to the traditional belief of “domestic shame should not be made public”. Secondly, this study will not conduct further follow-up after three months’ intervention due to the time and financial restrictions. Thirdly, some potential biases could be caused as blinding of researchers during the whole research process is not possible.

## 4. Conclusions

It will be the first study to test the effects of an OTO intervention for the prevention of PPD among rural-to-urban Chinese floating women. This innovative format of intervention could possibly reduce financial and time costs in health care systems, increase the efficacy and outcome of mental health services, and promote help-seeking behaviors of Chinese floating women after childbirth. If the “Hi, Mom” intervention is verified to be effective in the prevention of PPD, this will not only provide a convenient intervention program for postpartum mental well-being among rural-to-urban floating women, but also will provide evidence-based knowledge for PPD clinical practice based on online and offline health technologies to save mental health service resources. Moreover, the outcomes gained from this study could be used to plan a culturally appropriate OTO intervention for other groups of postpartum women, such as migrant mothers from different countries, single mothers, and city resident women.

## Figures and Tables

**Figure 1 ijerph-19-07951-f001:**
[figure not shown]
CONSORT flowchart of the study.

**Figure 2 ijerph-19-07951-f002:**
[figure not shown]
The theoretical framework of the “Hi, Mom” intervention.

**Table 1 ijerph-19-07951-t001:** The details of the “Hi, Mom” program.

Items	Intervention Group	Control Group
Brief name	“Hi, Mom” + routine care	Routine care
Who provided	Researchers	Obstetricians, obstetric nurses, community doctors
Where	Web environment, home	Hospital, home
How (medium)	Online intervention by internet Offline intervention by face-to-face	Routine care by face-to-face
What	Information module; communication module; ask-the-expert module; peer story module; and face-to-face consulting.	Routine postpartum care, home visiting.
How long and how often	From childbirth to 3 month postpartum. The total intervention time not less than 12 weeks. Reminder telephones every week, reminding them to log in the online session at least twice a week, and no less than total 1 h per week; and attending 2 face-to-face consulting meetings, about 30–45min each time.	From childbirth to 1 month postpartum. At least 2 home visits.
When assessed	Baseline (preintervention) Postintervention (immediately after intervention) Follow-up (three months after intervention)	Baseline (preintervention) Postintervention (immediately after intervention) Follow-up (three months after intervention)

**Table 2 ijerph-19-07951-t002:** The study variables and assessment times.

Variables	Baseline (T0)	Postintervention (T2)	Three Months Follow-Up (T3)
Sociodemographic and clinical data	※		
Postpartum depression symptoms	※	※	※
Postpartum depression stigma	※	※	※
Social support	※	※	※
Quality of life	※	※	※
Mother–child bonding	※	※	※
Satisfaction with health care received		※	

T0: before randomization; T1: immediately after the intervention; T3: three months after the intervention.

## Data Availability

Not applicable.
